### Analysis

Personnel analysing the data from this trial will be blinded to group allocation. A total of 600 Corrective Services Personnel will be included in the trial. Power calculations were conducted using GPower 3.1.9.7 to determine the between treatment condition effect at follow-up on the premise of a small effect size. This calculation indicated a minimum sample size of 270 participants per group (power = 0.95, alpha = 0.05, two-sided). On the basis of 10% attrition at follow-up, it was estimated that 600 participants (300 per group) were needed.

Analyses will focus primarily on intent-to-treat analysis. Using SPSS version 28, hierarchical linear mixed models will be used to study differential effects of each treatment condition because this method effectively handles missing data by calculating estimates of trajectories. Fixed (intervention, time of assessment) effects and their interactions will be considered in the unstructured models, which will provide an index of the relative effects of the treatments; time of assessment will include baseline, posttreatment, and 3-month follow-up. For the follow-up analyses between the two conditions, analyses will focus on linear time effects, treatment conditions, and interactions. Fixed effects parameters were tested with the Wald test (t-test, *p* < 0.05, two-sided) and 95% confidence intervals. Cohen’s (d) effect size was calculated for all analyses. The primary outcome measure will be the K10. The primary outcome timepoint will be the 6 months assessment. As baseline assessments are incorporated into this modelling, the likelihood of no data is zero. To this end, missingness will be tested at random by assessing baseline characteristics of those do and do not drop out from the study.

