### Randomization

Prison personnel within eight prison settings across NSW will be allocated to either the resilience program or no control intervention on a 1:1 basis (no block randomization). This will be carried out on a computerized software by a research assistant who is independent to any other aspects of the intervention. This randomization will take place prior to the completion of the T0 assessment. No blinding will be used for the participants and clinical psychologists delivering the interventions.

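### The stated 95% power with 270 per group fits an effect of about d = 0.31; at the conventional small effect of d = 0.2, unadjusted power is about 64%, and the article gives no effect size, test or correlation to settle which was meant

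*Protocol article*

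**What the plan says.** The Analysis section of the protocol article names the software and the comparison: "Power calculations were conducted using GPower 3.1.9.7 to determine the between treatment condition effect at follow-up". The premise is only a size label: the calculation was run "to determine the between treatment condition effect at follow-up on the premise of a small effect size". The result and the error rates come in one sentence: "This calculation indicated a minimum sample size of 270 participants per group (power = 0.95, alpha = 0.05, two-sided". Attrition is then added: "On the basis of 10% attrition at follow-up, it was estimated that 600 participants (300 per group) were needed". The Randomization section sets allocation "on a 1:1 basis (no block randomization").

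The same Analysis section plans a linear mixed model that includes the baseline assessment, and names Cohen's d as the effect-size measure for all analyses. It does not give a value of d, a standard deviation, the G*Power test family, or a correlation between repeated K10 measurements.

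**The concern.** The article prints every input to a two-group calculation except the one that decides the answer. With the effect described only as small, and Cohen's d as the trial's measure, most readers will supply d = 0.2. At that value the printed sample size and the printed power do not go together.

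This is more than a detail left to a fuller document. The article itself publishes software, power, alpha, sidedness and sample size, and these do not agree with the usual meaning of the premise they are attached to.

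A power of 95% tells readers that a small effect, if real, would be missed one time in twenty. If the true effect is about 0.2, the unadjusted risk of missing it is about 36%. An effect of that size is plausible for a two-session preventive programme that does not require distress at entry. A null result would then say less about a small benefit than the stated power suggests, and the Discussion looks ahead to wider roll-out on the strength of this trial.

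**Working it through.** **Inputs from the article.** Two-sided alpha 0.05; power 0.95; 1:1 allocation; 270 per group before attrition; 10% attrition. **Assumption, not in the article:** d = 0.2 as the conventional small effect, with a range shown below.

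**Step 1. Attrition.** 270 / (1 − 0.10) = 300 per group, 600 in total. This reproduces, so the question lies with the 270.

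**Step 2. Sample size at d = 0.2.** Normal approximation for two means:

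n per group = 2 (z₀.₉₇₅ + z₀.₉₅)² / d² = 2 (1.960 + 1.645)² / 0.04 ≈ 650.

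The exact noncentral t calculation gives 651. For 90% power it gives 527, and for 80% it gives 394. A one-sided test at 95% power would need 542. None of these is near 270.

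**Step 3. Power of 270 per group at d = 0.2.** The noncentrality is 0.2 × √(270/2) = 2.324. Then Φ(2.324 − 1.960) = Φ(0.364) ≈ 0.642, and 0.640 by noncentral t. With no attrition (300 per group) the noncentral t figure is 0.686.

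**Step 4. The effect at which the stated figures agree.** d = (1.960 + 1.645) × √(2/270) ≈ 0.310, and 0.311 by noncentral t. This is about half as large again as 0.2 (0.311 / 0.2 ≈ 1.55). At 270 per group, 90% power is reached at d = 0.28 and 80% at d = 0.24.

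| Assumed d | n per group for 95% power | Power at 270 per group |
|---|---|---|
| 0.20 | 651 | 64% |
| 0.25 | 417 | 83% |
| 0.30 | 290 | 94% |
| 0.31 | 272 | 95% |
| 0.35 | 214 | 98% |

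**Step 5. Baseline adjustment at d = 0.2.** Adjusting for T0 K10 multiplies the outcome variance by 1 − ρ², so the effective d is 0.2 / √(1 − ρ²). The correlations are assumed values.

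| ρ | Effective d | Power at 270 per group |
|---|---|---|
| 0.5 | 0.231 | 76% |
| 0.6 | 0.250 | 83% |
| 0.7 | 0.280 | 90% |

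For 95% power, 651 (1 − ρ²) = 270 gives ρ = √(1 − 270/651) = 0.765, or about 0.77.

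**Step 6. Repeated-measures routes.** G*Power also offers repeated-measures F tests, for which the conventional small effect is f = 0.1. With a total of 540 (2 × 270):

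- Group-by-time interaction, two measurements: 94.5% power at correlation 0.15 and 95.6% at 0.20.
- Between-group factor, three measurements: 95.6% at correlation 0.10.
- Group-by-time interaction, three measurements: 95.8% at correlation 0.

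Such settings could have produced a figure near 270 per group. An interaction of f = 0.1 with two measurements is a larger effect than d = 0.2 at follow-up: it puts each cell 0.1 SD from additivity, a difference in change of 4 × 0.1 = 0.4 SD, and so a follow-up difference of 0.4 SD if the groups start equal.

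**The case against.** A reader might infer that the sample-size statement is simply wrong: that the trial claims 95% power and has 64%. The article does not support that. The value 0.2 is nowhere in it. The stated sample size, power and alpha agree with one another at d of about 0.31, which some authors would still call small. Nor is a baseline correlation near 0.77 the only way to reach 270 from a small effect, because Step 6 shows low-correlation repeated-measures settings that come close. This part of the objection stands, so the origin of 270 cannot be identified from the text.

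It does not vindicate the figure. No correlation is stated, values of 0 to 0.20 are doubtful for repeated K10 scores in the same people, and the text describes a between-condition effect at follow-up, not an interaction.

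A second inference is that the trial would miss a small effect about a third of the time. That applies only to d = 0.2 with no gain from baseline. The planned mixed model includes T0, so the actual miss rate depends on an unstated correlation; with covariate adjustment at ρ = 0.7 it would be about 10%. The article also commits to 95% confidence intervals and Cohen's d, which would show what a null result excludes and so limit the risk of over-reading it. Both points stand and lower the weight of the concern.

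**Conclusion.** The point holds as a mismatch that has to be reconciled, not as a proven calculation error. For a two-sided two-sample comparison at follow-up, 270 evaluable per group supports 95% power at d of about 0.31. If *small* means d = 0.2, unadjusted power is about 64%, a shortfall of 31 percentage points. With baseline adjustment, power would be 76% to 90% for assumed correlations of 0.5 to 0.7, still short of 95%.

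These figures rest on independent observations, equal groups, and d = 0.2 as the meaning of the label; the last is a convention and not a statement in the article. Sample size, allocation and analysis are unaffected. This should be fixed, but it does not threaten the validity of the trial.

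**What to change.** Keep N = 600. In the sample-size paragraph, state the numeric effect size, the G*Power test family and any correlation actually used, so that 270 can be reproduced. Then report what the sample delivers, whatever the source of the 270, for example:

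> *270 evaluable participants per group give 95% power for d = 0.31 and 80% power for d = 0.24 (two-sided alpha 0.05); power for d = 0.20 is 64% without baseline adjustment.*

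If a baseline correlation was assumed, give its value and make sure the primary model uses T0 K10 in a way that delivers the gain. A group-by-time contrast that leaves the T0 means free behaves like a change-score analysis, with variance factor 2(1 − ρ). At ρ = 0.5 that factor is 1, so there is no gain, whereas covariate adjustment gives 1 − 0.25 = 0.75.

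The cost is a sentence or two and a less favourable stated figure. No extra participants are needed.

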### Design & setting

This study is designed as a parallel RCT that will be conducted in prisons across NSW in Australia. The study will deploy a 2 (Treatment condition) × 3 (Assessment Point) factorial design. Participants will be assessed at baseline (T0),, at two-month follow-up (T1), and at six-month follow-up (T2), where T1 will be the primary outcome timepoint (see Fig. 1). This trial was registered on Australian New Zealand Clinical Trials Registry (ACTRN12622000029796) on 14 January 2022 and received ethical approval from the University of New South Wales Human Ethics Panel C, Australia. The Resilience Program will provide 2 × 2-h sessions administered by clinical psychologists one month apart, delivered in groups of 10–15 people.

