#### No intervention

The control condition will engage in repeated assessments across T0, T1, and T2.

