### Data oversight & management

Study implementation procedures will be monitored on an ongoing basis by the trial management committee consisting of the principal investigator, co-investigators, and local research coordinators. All adverse events that take place during the trial will be monitored by the facilitators at each session, whereby any reported adverse events will be referred to the UNSW Human Ethics Committee and Trial Sponsor. Further, assessments using the K10 were used to detect severe distress and relevant participants were contacted and recommended referral resources.

All participants will be required to have their identities known to the study as they will be followed up for trial assessments at two- and six-month follow-up assessments (T1 & T2). All data from pre-treatment, and follow-up online surveys will be entered on an electronic database in a deidentified manner in which participants are allocated a unique identification number. Restricted access will be made available to research staff directly involved in the study. AES-256 bit encryption will be used move any data from one electronic location to another. The research staff working on the project will initially have access to the data via the UNSW Research Long Term Data Store Interface. Any study protocol amendments will be approved by the local ethics committee prior to implementation. All investigators and participants enrolled in the trial will be informed.

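### The mixed model's listed time levels do not match the trial's visits, and under the linear-time comparison it describes no tested parameter is the arm difference at 2 or 6 months

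*Protocol article*

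**What the plan says.** Three places in the protocol article agree on the visits. Design & setting puts the follow-ups "at two-month follow-up (T1), and at six-month follow-up (T2". Data oversight & management says participants are "followed up for trial assessments at two- and six-month follow-up assessments (T1 & T2". The No intervention section says "The control condition will engage in repeated assessments across T0, T1, and T2".

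The Analysis section departs from this. It first describes the model: "Fixed (intervention, time of assessment) effects and their interactions will be considered in the unstructured models". The same sentence then gives the levels: "time of assessment will include baseline, posttreatment, and 3-month follow-up". The next sentence says: "For the follow-up analyses between the two conditions, analyses will focus on linear time effects, treatment conditions, and interactions". Fixed-effect parameters are to be tested with Wald tests at the two-sided 0.05 level.

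On the primary timepoint, the Abstract (2 months post intervention) and Design & setting (T1) point to 2 months. The Analysis section names the 6-month assessment.

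**The concern.** The analysis rule names time levels that are not the trial's visits. It leaves out the 6-month visit, which the same section calls primary.

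The way time enters the model is also unsettled. One sentence suggests a factor with discrete levels, while the next points to a straight line for the comparison between arms. The two can give different estimates of the effect at a visit from the same data. If the choice stays open, the primary result could depend on a decision made after the data are seen. If the straight line is used, the test addresses a difference in monthly slope, whereas the protocol states its primary outcome at a visit.

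**Working it through.** **Step 1. Visit lists side by side.**

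| Design & setting, No intervention, Data oversight & management | Analysis |
|---|---|
| T0, baseline | baseline |
| T1, 2 months | posttreatment (not defined; may mean T1) |
| T2, 6 months | not listed |
| no such visit | 3-month follow-up |

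Only baseline matches by name.

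**Step 2. What a linear-time model tests.** Let D(t) be the arm difference in mean K10 at month t. With linear time, D(t) = a + bt. The treatment term is a, the arm difference at time zero. The treatment-by-time term is b, the difference in slope. The effects at the visits are D(2) = a + 2b and D(6) = a + 6b. Both can be derived from the fit, but neither is one of the tested parameters.

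**Step 3. When the derived value is right.** Code the visits as months 0, 2 and 6, and let y be the true arm differences at those visits. Three points fitted by a line leave one residual direction, c = (2, -3, 1): its entries sum to 0, and 0(2) + 2(-3) + 6(1) = 0. For covariance matrix V, generalised least squares gives

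fitted = y - Vc (c'y)/(c'Vc).

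If y is linear over the three months, then c'y = 0 and the fit is exact. For example, y = (0, -d/3, -d) gives c'y = d - d = 0.

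Under compound symmetry Vc is proportional to c, so fitted = y - c (c'y)/14, where 14 = 4 + 9 + 1. The within-person correlation cancels.

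**Step 4. Illustrations.** The protocol gives no expected course, so these profiles are assumptions.

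- Sustained effect, y = (0, -d, -d): c'y = 3d - d = 2d. The residual is (2, -3, 1) × 2d/14 = (0.286, -0.429, 0.143)d, so the fitted values are (-0.286, -0.571, -1.143)d. The T1 effect is 43% too small and the T2 effect 14% too large.
- Effect gone by T2, y = (0, -d, 0): c'y = 3d. The residual is (2, -3, 1) × 3d/14 = (0.429, -0.643, 0.214)d, so the fitted values are (-0.429, -0.357, -0.214)d. The slope is (-0.214 + 0.429)d/6 = +0.036d per month. Its sign points away from benefit.

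**Step 5. Dependence on the covariance.** Take equal variances and assumed correlations of 0.6 (T0, T1), 0.6 (T1, T2) and 0.4 (T0, T2). Then Vc = (0.6, -1.2, 0) and c'Vc = 1.2 + 3.6 + 0 = 4.8.

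- Sustained: the T1 residual is -1.2 × 2d/4.8 = -0.5d, so the fitted T1 effect is -0.50d. At T2 the fit is exact.
- Gone by T2: the T1 residual is -1.2 × 3d/4.8 = -0.75d, so the fitted T1 effect is -0.25d.

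The exact figures move with the covariance. The attenuation at T1 is not produced by compound symmetry.

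**The case against.** Posttreatment has a reasonable reading. The two sessions are one month apart, so a 2-month visit falls after treatment. A reader might infer from the list that two of the three levels are never collected and that the model cannot be fitted. The documents do not support that: three levels fit three visits once relabelled. The relabelling does not rescue the 3-month level or the missing 6-month visit.

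The sentence on unstructured models lists discrete assessment times and reads naturally as categorical time, which would give an arm contrast at each visit. The scope of the linear-time sentence is unclear. A reader might infer that the trial is bound to test a slope and will not estimate the effect at its primary visit. That is too strong. What stands is that the comparison between conditions is tied to linear time in words, and that the two sentences are not reconciled. An article may leave the exact contrast to an analysis plan, but here it states the time levels itself, and states them wrongly.

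The trajectories are assumed. The app stays available throughout the study, so an effect that grows is possible, and linear growth from baseline would be recovered exactly. The figures in the working are therefore scenarios and not predictions.

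**Conclusion.** The mismatch in visits is a plain contradiction in the current text and has to be corrected. The linear-time point holds in a narrower form: under linear time no tested parameter is the arm difference at 2 or at 6 months, and the implied value is right only if the arm difference is linear over months 0, 2 and 6. The sizes (-0.57d and -1.14d for a sustained effect; -0.36d at T1 with a wrong-signed slope for an effect gone by T2) rest on assumed profiles, on visits coded as months 0, 2 and 6, and on compound symmetry.

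Two further inferences are tempting. One is that T1 is the primary visit and the main harm is a missed benefit there. The documents conflict on the primary visit. If it is T2, the sustained profile gives an overstatement instead. The other is that the model is at fault for not adjusting for baseline K10. That would be an efficiency gain under an assumed effect size and correlation, not the correction of an error. The Randomization section also places allocation before T0 is completed and leaves participants unblinded, so adjustment is safe only if T0 K10 is collected before participants learn their allocation. It is no part of this point.

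**What to change.** In the Analysis section:

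- Define time as a categorical factor with levels T0, T1 (2 months) and T2 (6 months), with an unstructured covariance across visits.
- Reconcile the 2-month statements (Abstract, Design & setting) with the 6-month statement (Analysis) so that one primary timepoint remains.
- Name the treatment-by-visit contrast at that timepoint as the primary test.
- Remove linear time from the confirmatory comparison.

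The cost is wording and one extra time parameter with its interaction. No additional data are needed.

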**Methods:**

A, parallel, randomized controlled trial will be carried out in a small group format. Following informed consent, corrective personnel within prisons across NSW will volunteer to either attend a clinician delivered resilience program on stress management skills or not (*N* = 600). The primary outcome will be change in psychological distress including anxiety and depression at 2-months post intervention. Secondary outcomes include help-seeking behaviours and absenteeism.

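### The primary timepoint for the K10 is two months in the Abstract and Design but six months in the Analysis, and the Analysis lists model visits that do not match the schedule

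*Protocol article*

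**What the plan says.** The article states the primary timepoint three times.

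- Abstract, Methods paragraph: "The primary outcome will be change in psychological distress including anxiety and depression at 2-months post intervention".
- Methods, Design & setting: participants are assessed at baseline (T0), then "at two-month follow-up (T1), and at six-month follow-up (T2), where T1 will be the primary outcome timepoint".
- Methods, Analysis: "The primary outcome timepoint will be the 6 months assessment".

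The measure is not in dispute. Aims & hypotheses and Primary outcome both name the K10, and the Analysis section repeats it: "The primary outcome measure will be the K10".

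The Analysis section also lists the visits that enter the mixed model: "time of assessment will include baseline, posttreatment, and 3-month follow-up". Data oversight & management gives the same schedule as Design & setting, with T1 at two months and T2 at six.

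**The concern.** The primary timepoint decides which single between-arm comparison carries the trial's 5% error rate. Here one section gives that role to T1 and another to T2. After the data are in, either result could be presented as the pre-specified primary one, with the article's text in support. The article states no multiplicity control across the two visits.

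The choice also changes the question. A two-month contrast asks about an effect soon after a two-session programme. A six-month contrast asks whether any effect lasts.

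The list of model visits adds to the problem. It contains no six-month visit, although the same paragraph names six months as primary. It contains a three-month visit that the schedule does not have. So the Analysis section cannot be relied on to settle which statement is right.

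**Working it through.** **Statements side by side**

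| Section | Visits after baseline | Primary timepoint |
|---|---|---|
| Abstract, Methods | not listed | 2 months, counted from the intervention |
| Design & setting | T1 = 2 months, T2 = 6 months | T1 |
| Data oversight & management | T1 = 2 months, T2 = 6 months | not stated |
| Analysis | post-treatment, 3 months | 6 months |

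Under the Design definitions the six-month assessment is T2, so the Analysis statement contradicts the Design statement. It is not worded as secondary or additional. All of this is current text, and the measure is the same, so the statements cannot be read as separate primary outcomes.

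**Does the sample-size text settle it?** It uses "power = 0.95, alpha = 0.05, two-sided", with 270 per group and 10% attrition. The attrition step reproduces: 270 / (1 − 0.10) = 300 per group, 600 in total. But both the effect and the attrition are given only at follow-up, with no visit named, so the calculation fits either timepoint.

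**What is at stake if the choice is free.** Inputs: two tests, each two-sided at 0.05 (from the Analysis section), with no true effect at either visit. The correlation r between the two test statistics is not given in the article, so every value of r below is an assumption.

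- Independent tests (r = 0): 1 − (1 − 0.05)² = 1 − 0.9025 = 9.75%.
- Perfectly correlated tests (r = 1): the two tests are one test, so 5%.
- In between: 1 − P(|Z1| ≤ 1.96 and |Z2| ≤ 1.96), with Z1 and Z2 bivariate normal with correlation r.

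| Assumed r | Chance of at least one false positive |
|---|---|
| 0 | 9.75% |
| 0.3 | 9.51% |
| 0.5 | 9.07% |
| 0.6 | 8.75% |
| 0.7 | 8.35% |
| 0.8 | 7.81% |
| 1 | 5% |

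**The case against.** Four things can be said for the plan.

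- The trial was registered in January 2022, before recruitment began in March 2022, and the registration may fix the timepoint. This stands in part: it is the right place to look first, but its content is not in the article and it does not make the article consistent.
- The analysts are to be blinded to allocation. That protects the model fitting. It does not stop the primary label being assigned after the allocation is revealed.
- An article condenses a fuller protocol, and a statistical analysis plan may exist. That would excuse silence. It does not excuse two incompatible statements.
- The error-rate figures apply only if the primary result is chosen after being seen. This stands. Nothing in the article suggests that such a choice is intended, so the figures show the room left open and do not estimate an actual error rate.

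A reader might go further and infer that the origin of T1 also conflicts, with the Abstract counting from the end of the sessions and the Design section from baseline. Because the sessions are one month apart, that would move T1 by about a month. The article does not support this. Only the Abstract names an origin. Design & setting and Data oversight & management name none, and their silence is compatible with the Abstract.

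Nor does any section say that the arms are counted from different origins, so a claim that time since baseline is confounded with arm has no basis. Control assessments could be scheduled to matching dates. What remains is a query: a control arm with no sessions has no intervention end of its own, and the article does not say how its T1 is set.

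**Conclusion.** The contradiction stands and must be resolved. Two statements make the two-month assessment primary and one makes the six-month assessment primary, for the same measure, and nothing in the article decides between them. The model visits in the Analysis section are also wrong against the schedule.

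If either test could be chosen after the results are seen, the false-positive rate lies between 5% and 9.75%. It is about 8.8% at an assumed correlation of 0.6 between the two test statistics. The range rests on two two-sided 5% tests and a free choice between them. The point within the range depends on a correlation that the article does not give. The contradiction itself rests on no assumption.

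The origin of T1 is a point to clarify, not a demonstrated error.

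**What to change.** Before any unblinded analysis, and with the date recorded:

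1. Check which primary timepoint was registered.
2. State one primary timepoint identically in the Abstract, Design & setting and Analysis. Unless the registration says otherwise, this is T1, as the Abstract and Design section have it, with T2 secondary. If the registration names T2, change the Abstract and Design section instead.
3. Say in the Analysis section that the primary test is the between-arm K10 contrast at that visit.
4. Replace the model visits in the Analysis section with T0, T1 and T2.
5. As a query, state the origin from which T1 was actually counted and confirm that it gives the same time since randomisation in both arms. Describe the origin in use and do not set a new one: visits may have been scheduled since recruitment began in March 2022, and a new definition could misdescribe data already collected.

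Steps 1 to 4 change wording only. The price is that the visit not chosen becomes formally secondary.
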